**Inclusion criteria**

Sick babies’ resident on the neonatal unitThose whose parents/caregivers consent to the studyBabies on a shift where the nurse on duty has consented to observations.

**Exclusion criteria**

We will exclude the following babies:Babies who are severely ill and at risk of imminent death during observations of careBabies with congenital anomaliesBabies with surgical conditionsThose whose parents decline consent

##### Observational objective

For our secondary quality of care indicator analysis, our study population will be all neonates admitted to our 4 study facilities and a set of 8 non-intervention hospitals, 12 months before and 12 months after introducing supplemental newborn unit nurses. For this population, we will track the number of vital signs conducted in the first 48 h of admission and the change in newborn mortality. This data is available from the CIN database.

### Research plan

#### Intervention

The intervention to be evaluated is the addition of 3 extra nurses to selected resource-constrained newborn units for 12 months. All facilities experience very low nurse-to-patient ratios and other wider resource constraints including limited access to technology and material resources for patient care, although access to technologies has been improved by the NEST360 programme. The provision of 3 additional nurses reflects a potentially feasible nurse staffing improvement by health policymakers in a resource-challenged setting like that in Kenya and should constitute an improvement in the nurse staffing of between 17.6% and 37.5% in these units (Table 1).

#### Logic model

We developed a logic model (Fig. 2) to guide our thinking on the deployment of our intervention, identify assumptions and articulate how our intervention is likely to influence the study outcome. This model was structured around the Donabedian structure-process-outcome framework where health system structures are likely to influence processes which in turn influence health outcomes [21]. Our intervention changes a key element of structure, nurse staffing, and is likely to affect nurse-delivered care and subsequently neonatal outcomes through our hypothesised pathway (Fig. 2). Key assumptions that along the proposed causal pathway for our intervention to have the desired effect include: i) support for the new nurses from the existing nursing staff, ii) availability of equipment and other routine resources for nurses to conduct their activities, and iii) support from the hospital authorities and nursing service manager such that additional human resources are not diverted to other understaffed parts of the hospital. To help address the last concern we sought agreements that hospitals would not divert human resources from the NBU to other hospital units following the addition of supplemental nurses and that they might replace any nurses who leave the unit. Additionally, the supplemental nurses will be trained in the provision of essential newborn care using approaches developed by the NEST360 programme and offered to existing hospital staff. To support the intervention a memorandum of understanding with the county governments of our intervention hospitals was signed.

**Fig. 2 Fig2:**
[figure not shown]
Logic model for the intervention

#### Intervention fidelity

From our logic model, we identified 3 key mediating variables that are useful measures of intervention fidelity i.e., variables that measure the magnitude or intensity of our intervention (Fig. 2). These variables are process variables and measure the time available for delivering nursing care. These metrics include:The total number of nursing hours per month assessed as the cumulative total number of nursing hours delivered per monthNursing hours provided per patient day assessed as the total nursing care hours provided to patients in a month/ Total number of patients admitted during the same defined periodNursing hour per patient per shift which is the total registered nursing shift hours divided by the total number of patients at the beginning of a shift.

If the intervention is deployed in the proposed manner, all three variables are likely to increase post-intervention with the first two metrics assessing broad changes in staffing and the third focused on specific periods including those that are subject to direct observation.

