**Methods:**

This prospective workforce intervention study will involve a multi-method approach. We will conduct a before and after study in newborn units of 4 intervention hospitals and a single time-point comparison in 4 non-intervention hospitals to determine if there is a change in the level of missed nursing care, a process measure of the quality of patient care. We will also determine the effect of our intervention on routinely collected quality indicators using interrupted time series analysis. Using three nurse staffing metrics (Total nursing hours, nursing hours per patient day and nursing hours per patient per shift), we will describe the relationship between staffing and the quality of patient care.

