#### Secondary objectives

2.To examine the degree to which additional staff affects nurse staffing metrics on Kenyan newborn units, as a measure of intervention fidelity, and the relationship between these metrics and missed nursing care on these wards.

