#### Primary and secondary objective (how supplemental nurse staffing impacts the level of missed nursing care)

Using bedside observations of care, we will employ a before and after design in 4 intervention hospitals selected from the 12 NEST360 hospitals. Our baseline observations will be conducted in the 4 intervention hospitals before enhancing nurse staffing and additional observations will be performed after 6 months. At the same post-intervention time point observations will be made in a further set of 4 hospitals from the original 12 that have not received the workforce intervention (Fig. 1). Our primary analysis will be the before-and-after within-site comparison, the single time-point observations in the 4 non-intervention sites will serve as an external reference for our 4 intervention hospitals. Data on nurse staffing metrics will be collected for 6 months before the workforce enhancement and in the 6 months leading to the post-intervention assessment in the 4 intervention hospitals. These data will be used to assess whether and to what degree providing additional nurses changes nurse staffing metrics as an indication of intervention fidelity. Similar data on nurse staffing metrics will be collected from the 4 reference hospitals and then data from all 8 hospitals at the post-intervention time point will be used to address our secondary objective of exploring the relationship between nurse staffing metrics and nurse-delivered care.

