### Site selection and eligibility criteria

We have selected solely public district-level health facilities that are part of the CIN and that have received a standard set of neonatal equipment and linked technical training as part of the NEST360 programme as study sites. Previous research has shown that these types of public hospitals experience the greatest level of missed nursing care associated with poor staffing levels [17]. Intervention sites are selected to be within 1 to 3 h of the Kenyan Capital, Nairobi because of travel restrictions linked to the Covid-19 pandemic enabling feasible access to these research sites. Table 1 provides a comparison of the staffing numbers and average admissions for the 4 intervention sites.

**Table 1 Tab1:** Bed capacity, annual admissions, and staffing strengths across the 4 intervention hospitals

Metric	Hospital A	Hospital B	Hospital C	Hospital D
Newborn unit bed capacity^a^	53	50	38	47
Nurse staffing numbers (pre-intervention)	17	11	10	8
Expected percentage change in nurse staffing after adding 3 extra nurses (%)	17.6	27.3	30.0	37.5

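### The metric labelled nursing hours per patient day is defined as nursing hours per patient admitted, so differences in length of stay can distort a fidelity measure and secondary exposure

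*Protocol article*

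**What the plan says.** The Intervention fidelity section states that "we identified 3 key mediating variables that are useful measures of intervention fidelity" and defines each of them. The first is total nursing hours per month. The second is labelled as hours per patient day and computed as "total nursing care hours provided to patients in a month/ Total number of patients admitted" over the same period. The third, hours per patient per shift, is "total registered nursing shift hours divided by the total number of patients at the beginning of a shift".

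The Abstract lists the same three metrics ("Total nursing hours, nursing hours per patient day and nursing hours per patient per shift") as the means of describing how staffing relates to quality of care. The secondary objective has two parts: how far the added staff change these metrics, as a measure of fidelity, and "the relationship between these metrics and missed nursing care on these wards". The Study design section adds that "data from all 8 hospitals at the post-intervention time point will be used to address our secondary objective". No other section gives a different definition of the second metric.

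**The concern.** The label and the formula describe different quantities. A count of patients admitted in a month gives the same weight to a baby who stays one day and one who stays thirty. Nothing in the formula (no daily census, bed-days or length of stay) turns that count into patient-days.

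Two uses are exposed. As a fidelity measure, the metric is meant to show whether nursing time per patient rose after three nurses were added; a change in length of stay between periods would make it differ from the quantity it is named after. As an exposure across 8 hospitals, it compares units that may turn patients over at different rates, so part of the variation between hospitals could be length of stay and not staffing. The third metric does use a census, so the plan already contains the kind of denominator that the second one lacks.

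**Working it through.** **Plan's own figure.** The expected staffing gain is 3 divided by baseline nurses: A 3/17 = 17.6%, B 3/11 = 27.3%, C 3/10 = 30.0%, D 3/8 = 37.5%. This matches Table 1 and the stated range of 17.6% to 37.5%.

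**Relation between the two quantities.** Patient-days ≈ admissions × mean length of stay. Therefore hours per admission = hours per patient-day × mean length of stay. This step needs no assumption about the hospitals.

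**Inputs for the illustration.** From Table 1, for A, B, C, D: nurses 17, 11, 10, 8; annual admissions 2357, 2514, 1299, 1800; beds 53, 50, 38, 47. Two inputs are assumed because the article does not give them:
- 160 hours per nurse per month. This cancels in every ranking and ratio.
- Census equal to bed capacity in every hospital, in place of the unstated census and length of stay.

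**Formulas (pre-intervention).** As written: nurses × 160 ÷ (annual admissions/12). Per bed-day: nurses × 160 ÷ (beds × 365/12). Implied stay: beds × 365 ÷ annual admissions.

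| | A | B | C | D | Ranking |
|---|---|---|---|---|---|
| Hours per admission (as written) | 13.85 | 8.40 | 14.78 | 8.53 | C > A > D > B |
| Hours per bed-day (proxy) | 1.69 | 1.16 | 1.38 | 0.90 | A > C > B > D |
| Implied stay, days | 8.2 | 7.3 | 10.7 | 9.5 | |

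With three nurses added, the values are 16.29, 10.69, 19.21, 11.73 per admission and 1.99, 1.47, 1.80, 1.23 per bed-day. The two rankings are the same as before.

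**Sensitivity to length of stay.** D and B change order if D's stay exceeds B's by a factor of 1.02 before the intervention (1.10 after). C and A change order at 1.07 (1.18 after). The other four pairs need ratios between about 1.4 and 1.8.

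**Sensitivity to occupancy.** If occupancy differs, the per-patient-day ratio D/B becomes (8/47)/(11/50) × (B's occupancy ÷ D's) = 0.77 × that ratio. The D/B reversal therefore disappears once B's occupancy is at least about 1.29 times D's. For A and C, (17/53)/(10/38) = 1.22, so that reversal disappears once A's occupancy is at least about 1.22 times C's. After the intervention the thresholds are lower: (14/50)/(11/47) = 1.20 and (20/53)/(13/38) = 1.10.

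**Before-after use, admissions held constant.** The written metric changes by (nurses + 3)/nurses whatever the length of stay. Hours per patient-day change by that factor divided by the change in stay. If stays lengthen by 10%:

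| | A | B | C | D |
|---|---|---|---|---|
| Written metric | +17.6% | +27.3% | +30.0% | +37.5% |
| Hours per patient-day | +7.0% | +15.7% | +18.2% | +25.0% |

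If admissions and length of stay are both unchanged, the two rows agree.

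**The case against.** The strongest reply is that little depends on this one metric. Total monthly hours show directly whether nursing time was added, and hours per patient per shift, the metric closest to the observed shifts, is correctly built. The Nursing Care Index comparison and the sample size do not use the second metric at all. All of this stands, and it limits the severity.

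A second reply is that *patients admitted* may loosely mean patients on the unit. If it meant average census, the result would differ from hours per patient-day only by the number of days in the month. But the text specifies a total over the period, and a total count of individuals, whether newly admitted or resident, is not patient-days.

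A reader might also infer more than the article supports:

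- *That A > C > B > D is the true ranking, with D 23% worse staffed than B (0.77).* This rests on equal, full occupancy. The Table 1 footnote reports cot sharing and admissions beyond capacity, by an unstated amount that may differ between hospitals. Equal length of stay would itself imply occupancy ratios of 1.31 (B to D) and 1.30 (A to C), and both metrics would then rank the hospitals identically.
- *That a 7- to 11-fold inflation measures the harm.* A common scale factor cancels in a percentage change and does not create or remove an association. Only variation in length of stay matters, and the article gives no figure for it.
- *That a change in stay both leaves the metric unmoved and hides or mimics the staffing gain.* The first needs constant admissions. The second needs a constant census, so that shorter stays mean more admissions. The article fixes neither, and the two statements should not be combined.
- *That the corrected denominator is already being collected.* No section says that shift-start counts are recorded for every shift of both 6-month windows.

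**Conclusion.** The mismatch between label and formula is certain and needs no assumption: as written, the metric is nursing hours per admission. Its consequence is conditional. It can misrank hospitals, and two of the six Table 1 pairs are close enough for modest differences in length of stay to reverse them; whether they are reversed cannot be settled without length of stay or census. It can overstate the gain per patient-day if stays lengthen while admissions hold, for example +17.6% shown against +7.0% in Hospital A for stays 10% longer. With stable length of stay, the within-hospital percentage change is correct on either denominator.

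Severity is moderate, limited to one fidelity measure and one exposure in the secondary objective. A reader might take this as a flaw that undermines the trial's main result. It does not: the primary comparison, the sample size, total nursing hours and hours per patient per shift are all unaffected.

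**What to change.** Redefine the second metric as total nursing hours in the month divided by total patient-days in the same month, where patient-days are the sum of the daily inpatient census. Two sources are possible:

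- shift-start patient counts, if they are recorded on every day of both 6-month windows, which the sponsor should confirm; or
- patient-days derived from routine admission and discharge data, if those dates are available for the 8 hospitals.

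If neither is available, rename the metric nursing hours per admission wherever it appears and do not interpret it as hours per patient day.

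The change is one line of definition plus some extra data handling to build monthly patient-days. The design, the primary analysis and the sample size stay as they are.

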#### Outcomes

##### Primary outcome

For our primary objective (how supplemental nurse staffing impacts the level of missed nursing care), our outcome will be the change in the magnitude of missed nursing care, which will be measured as a change in a Nursing Care Index (NCI). The NCI is an unweighted aggregate patient-level score of all the items of care that are delivered to a baby compared with all the items of expected care [17]. A lower NCI score means more care is missed while a higher score means more care is carried out by nurses for the baby.

Missed nursing care is a process measure of the quality of care provided and it might be more sensitive to a change in nursing numbers [14]. Additionally, it is a direct marker of the nursing process and is an early precursor to adverse patient health outcomes [14].

##### Observational outcome

Data on the recording of vital signs by nurses (respiratory rate, heart rate, temperature, and pulse oximetry) is routinely collected as part of CIN activities. Prior research and unpublished observations show it is uncommon for these observations to be taken and recorded at the recommended minimum frequency of every 6 h for the first 48 h of admission, a problem at least in part attributed to poor nurse-to-patient ratios [22, 23]. An improvement in vital signs monitoring temporally associated with the intervention of enhancing nurse staffing would provide support for the hypothesis that better staffing improves care quality. Mortality is a distal outcome in our hypothesized causal pathway (Fig. 2) as it is likely to be affected by multiple influences (e.g. case-mix) [24]. Changes in mortality a measure of the effectiveness of our intervention and as an important outcome for policymakers will be examined in exploratory analysis.

#### Data collection tool

##### Missed nursing care data collection tool

To measure the level of missed nursing care before and after our intervention (our primary objective), we will employ an adapted version of the Nursing Care Index (NCI) tool [17] (Additional file 1). This tool involves performing non-participatory observations of nursing care provided to newborns using a structured checklist (supplementary material). Our adaptation to the existing tool includes key data on potential confounders of the relationship between nurse staffing and missed nursing care, for example, proxy data to estimate nursing workload on shifts (number of high acuity babies, babies on interventions such as Continuous Positive Airway Pressure), support staff available on shift, and presence of the necessary medical equipment for carrying out certain nursing duties such as pulse oximetry recordings. We will pilot our adaptation of the NCI tool for feasibility.

#### Observations of care

We will employ four observers across our 4 intervention sites to conduct bedside observations of care. These will be staff with a qualification in Allied Health Sciences, for example, nutrition science as proved successful in prior work [17]. We will avoid employing nurses or medical doctors as this group are likely to ascribe their professional standards to the care they are observing, and it would be challenging for them to retain non-participant status.

Because missed nursing care has previously been shown to vary across shift timing (day and night, weekday and weekend) and also patient severity [17], we will employ stratified data collection with the aim to equally distribute observations across the morning and night shifts and in a 5: 3 ratio across weekdays and weekends. This is carried out to maximise variation in the observational periods and to have a representative estimate of missed care across all shifts. Our stratified data collection will also involve conducting observations on babies with different illness severities (Fig. 3).

**Fig. 3 Fig3:**
[figure not shown]
Sampling approach across hospital facilities. 1 – Random Weekend Day 12-h shift, 2—Random Weekend night 12-h shift, 3- Random Weekday Day 12-h shift, 4- Random Weekday night 12-h shift. Weekend and weekday shifts are in a 5:3 ratio

#### Statistical power

Drawing on prior experience for our primary outcome [17], assuming a 5% improvement in mean NCI scores (SD- 15%), adjusting for clustering with a design effect of 1.5 and setting α and β at 5% and 80% respectively, the minimum sample size for this study will be 213 in each period (pre-intervention and post-intervention). This will be split equally across the 4 hospitals (55 babies in each hospital per period). This will further be split across randomly sampled 12-h weekday and weekend shifts and across illness severity categories (A, B, C) (Fig. 3). In each shift, we will aim to observe 4 co-located babies for the entire duration of the randomly sampled 12-h blocks. This has been deemed logistically feasible based on prior experience using the NCI tool within the same setting [17].

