### Statistical analysis

We will use summary statistics to describe our study's contextual data (e.g., monthly admission numbers, and patterns of diagnosis). To determine if there is a change in the level of missed nursing care across periods (pre-and post-intervention), we will use linear regression analysis with the NCI as the outcome variable and observation period as the main independent variable. Linear regression will also be used to assess the effect of intervention after adjusting for potential confounders such as patient severity category, and observation made on a weekend/weekday. We will report the risk ratios and corresponding 95% confidence intervals. For our secondary objectives, we will use interrupted time series analysis to track changes in the secondary quality indicators.

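### The power statement gives β as 80% although 213 per period needs β = 20%, and the stated primary regression does not carry the clustering that the sample size allows for

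*Protocol article*

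**What the plan says.** All the sample-size inputs are in the Statistical power section of the protocol article:

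- Effect and spread: "assuming a 5% improvement in mean NCI scores (SD- 15" percent).
- Error rates: "setting α and β at 5% and 80% respectively". Whether the test is one- or two-sided is not stated.
- Clustering: "adjusting for clustering with a design effect of 1.5". No intracluster correlation, cluster size or cluster level is given.
- Result: "the minimum sample size for this study will be 213 in each period (pre-intervention and post-intervention").
- Allocation: "This will be split equally across the 4 hospitals (55 babies in each hospital per period"), which makes 220 per period.
- Within-shift sampling: "In each shift, we will aim to observe 4 co-located babies".

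The Study design section makes the within-site before-and-after comparison in the four intervention hospitals primary. For that comparison the Statistical analysis section says "we will use linear regression analysis with the NCI as the outcome variable and observation period as the main independent variable". It then adds an adjusted regression, with illness severity and weekend or weekday as examples of confounders. It mentions neither hospital nor shift, and no allowance for correlated observations.

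**The concern.** There are two linked problems.

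First, the sentence that justifies the trial's size states an error rate that contradicts the sample size beside it. A reader who takes β at face value concludes that the trial has a one-in-five chance of detecting its target effect.

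Second, the sample size assumes that babies are correlated within some unit, while the model as written treats them as independent. If the correlation is real for the period contrast, the regression standard error is too small. The confidence interval is then too narrow and the chance of a false positive exceeds 5%. Two groupings are described, 55 babies per hospital and 4 per shift, and the text does not say which one the 1.5 stands for. The power that the planned number delivers therefore cannot be read off without a further assumption.

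**Working it through.** **Inputs** (Statistical power section): difference 5 points, SD 15 points, α 5%, design effect 1.5, 213 per period as a minimum, 4 × 55 = 220 planned, 4 babies per shift.

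**1. Reproduce the stated number.** Per period, n = 2(z₁₋α/₂ + z_power)² × SD²/difference², multiplied by the design effect.

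- Two-sided 5%, power 80%: 2(1.96 + 0.842)² × 15²/5² = 141.3, rounded up to 142; 142 × 1.5 = **213**. This matches exactly.
- Two-sided 5%, β = 80% (power 20%): 2(1.96 − 0.842)² × 9 = 22.5, rounded up to 23; 23 × 1.5 = 34.5, about 35. No match.
- One-sided 5%, power 80%: 112 × 1.5 = 168. No match.

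Of these readings only the first gives 213. The 80% is the power, and β should read 20%.

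**2. Power at the planned 220.** SE of the change = √(2 × 225 × 1.5/220) = 1.75. Then 5/1.75 = 2.85, and the normal-approximation power is Φ(2.85 − 1.96) = 81.4%. Using about 108 degrees of freedom (220/4 = 55 shifts per period, 110 in all, less 2), it is 80.8%.

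**3. Type I error of the model as written.** If the true variance of the period contrast is 1.5 times the variance that an independence model reports, the nominal 1.96 cut-off acts as 1.96/√1.5 = 1.60. The two-sided type I error is 2 × [1 − Φ(1.60)] = 0.1095, about **11%**. The nominal 95% interval would cover about 89%.

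**4. What the 1.5 could mean.** From design effect = 1 + (m − 1) × ICC:

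- shift, m = 4: ICC = 0.5/3 = 0.167;
- hospital, m = 55: ICC = 0.5/54 = 0.0093.

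**5. Power at 220 under different assumptions about the level.** None of these assumptions is stated in the protocol article.

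| Assumption | Power |
|---|---|
| Clustering by shift, no hospital-by-period variation | about 81% |
| All of the 1.5 is hospital-by-period variation, 6 df | 66.5% |
| All of the 1.5 is hospital-by-period variation, 4 paired changes, 3 df (critical t 3.18) | 49.7% (simulation 49.8%) |
| Shift design effect 1.5 plus an assumed hospital-by-period ICC of 0.005 to 0.02, 3 df | 44% to 33% |

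Hospital differences that are the same in both periods cancel in a within-site comparison. They do not take power below the first row.

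**The case against.** The strongest reply is that the β error is a labelling slip. The intended power can be recovered from the section's own inputs, and neither the number of babies nor their allocation changes. That is right, and nobody should infer that the trial was built with 20% power. The sentence is still wrong as published.

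The second reply is that this is a condensed article. Cluster-robust errors or random effects may be set out in a full protocol or analysis plan that is not shown, and the term linear regression does not exclude them. This also has force: silence on such detail would not be a finding. What remains is a mismatch between two things the article does state, a sample size enlarged for clustering and a named primary model with none.

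A reader might also infer that the 80% power holds only if the design effect is for shifts, or that the real power is about 50%. The article supports neither. The primary comparison is within site, so stable hospital differences drop out. The 50% figure needs the whole 1.5 to be hospital-by-period variation and a four-pair t-test that is not planned. The primary objective is framed around four hospitals, and Site selection shows that they were chosen partly for access, so they are not a random sample of hospitals. Nor can a shift-level ICC of 0.167 be attributed to the authors. It is only what 1.5 implies if the shift is the cluster.

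**Conclusion.** The concern holds in two parts.

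- **β is misstated.** It should be 20% (power 80%). This is certain, because 213 follows exactly from the other inputs at that value with a two-sided 5% test. The design is unaffected, and power at 220 is about 81% on the plan's own assumptions.
- **The design effect and the stated primary model do not agree.** Run as written, the test would have a type I error of about 11% instead of 5%. This assumes that the 1.5 is real for the before-after contrast and is not absorbed by the covariates. If the clustering were only stable hospital differences, or were largely explained by weekend or weekday, the inflation would be smaller or absent. Because the level of the 1.5 is unstated, the article does not settle which case applies.

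Power of about 50% belongs only in a caveat with its assumptions attached. It is not the power of the planned comparison. The model is the more important part, because it affects how a positive result is read; the β correction alone would be editorial.

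**What to change.** 1. In Statistical power, restate the basis as two-sided α = 5%, β = 20% (power 80%), 213 per period, rounded up to 220 (55 per hospital).
2. State whether the 1.5 refers to shifts or hospitals, with the correlation and cluster size behind it. The authors must supply this; it should not be inferred for them.
3. In Statistical analysis, specify the primary model with hospital as a fixed effect and shift as a random effect or shift-clustered standard errors. State that inference is conditional on the four hospitals.
4. Optionally, add a caveat on power with its assumptions: about 81% if clustering is by shift with no hospital-by-period variation; about 50% if all of the 1.5 is hospital-by-period variation tested on four paired changes with 3 df; lower if both levels contribute.

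The cost is a few sentences. No babies, observers or observation shifts are added. Standard errors will be wider than under an independence model wherever the shift clustering is real.
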